#### 2.4.4 Recovery from general anesthesia

All the drugs will be discontinued at the end of the surgery. A child who has regular spontaneous breathing and recovery of airway reflexes will be extubated and transferred to the post-anesthesia care unit (PACU) for continuing regular anesthesia monitoring, where an attending anesthesiologist who will be unaware of trial grouping will assess the level of sedation, ED, and pain.

After removal of the investigational drugs, MOAA/S scores will be assessed every 5 min for at least 40 min until 3 consecutive MOAA/S scores of 5. In group R, as long as no arousal occurs after 1 h from the end of remimazolam administration, 0.2 mg flumazenil will be given and a dose of 0.1 mg will be repeated as needed. ED and pain in PACU individually will be evaluated using the Pediatric Anesthesia Emergence Delirium (PAED) scale (Sikich and Lerman, 2004) (Supplementary Table S2)—a reliable tool in the diagnosis of ED and the face, legs, activity, cry and consolability (FLACC) scale (Crellin et al., 2018) (Supplementary Table S3)—a validated pain measurement tool for children aged 2 months to 7 years. Both scales will be recorded every 5 min for at least 30 min after the arrival of PACU. PAED scores ≥10 will be considered a diagnosis of ED and PAED scores ≥15 will be defined as a severe ED. A child considered to have developed delirium or moderate and severe pain (FLACC scale >3) will be treated with remedial sedatives and/or analgesic drugs (e.g., propofol or fentanyl) at the attending anesthesiologist’s discretion. The modified Aldrete score will be recorded every 3 min after 3 consecutive MOAA/S scores of 5, and the child will be admitted to discharge from the PACU until 2 consecutive modified Aldrete scores ≥9.

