
There are several similarities in terms of pharmacological and pharmacokinetic characterization between remimazolam and midazolam commonly given as intraoperative or preoperative agents for anxiety control as well as preventive therapy for ED in children (Urits et al., 2020). Other interesting findings have shown remimazolam besylate, compared with dexmedetomidine, was equally effective in relieving agitation in older patients aged ≥70 years following orthopedic surgery (Deng et al., 2022) and remimazolam provided a non-inferiority quality of recovery (QoR) on postoperative day 1 to propofol for general anesthesia in female patients aged 20–65 years undergoing thyroid surgery (Choi et al., 2022). The assessment of QoR on day 1 postoperatively depends on the QoR-15 questionnaire, which is a global measure of recovery after surgery. These outcomes should contribute to the holding of another hypothesis—remimazolam applied on induction and maintenance of general anesthesia could be identically effective in decreasing the incidence of ED and negative behaviors after hospitalization in preschool-age children to propofol.

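### The minimum window for scoring delirium and pain runs from PACU arrival, not from awakening, so a child who wakes late after arrival is guaranteed less awake observation

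*Protocol article*

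**What the plan says.** All the timing rules stand in section 2.4.4 of the protocol article.

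- Transfer: "A child who has regular spontaneous breathing and recovery of airway reflexes will be extubated and transferred to the post-anesthesia care unit (PACU"). Being awake is not a condition.
- Delirium and pain: "Both scales will be recorded every 5 min for at least 30 min after the arrival of PACU". This is a minimum with no stated end.
- Sedation: "MOAA/S scores will be assessed every 5 min for at least 40 min until 3 consecutive MOAA/S scores of 5", counted from the end of the study drug.
- Discharge readiness: "The modified Aldrete score will be recorded every 3 min after 3 consecutive MOAA/S scores of 5", and two consecutive scores of 9 or more are needed to leave.
- Late arousal: flumazenil is provided for in Group R "as long as no arousal occurs after 1 h from the end of remimazolam administration".

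Section 2.5 makes the incidence of delirium and of FLACC above 3 in PACU secondary endpoint 6, remedial drugs in PACU endpoint 7, and awakening time endpoint 4. Section 2.7 compares binary endpoints as crude proportions by chi-square or Fisher's test. The Discussion adds a second hypothesis, that remimazolam could be "identically effective in decreasing the incidence of ED and negative behaviors after hospitalization" to propofol.

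**The concern.** MOAA/S scoring continues until the child is awake, and Aldrete scoring starts only then. PAED and FLACC, which define endpoint 6, are tied to arrival alone. A child who arrives asleep uses up part or all of the required 30 min before delirium or awake pain behaviour can be seen.

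How much of the window is lost depends on how long the child sleeps after arrival, which the assigned drug may influence. Awakening time is itself an endpoint, so a difference between arms is an open question in this trial. If there is one, the two incidences rest on unequal awake time, and the planned tests do not adjust for that. The second hypothesis is one of similarity, and under-ascertainment in one arm could create similarity or hide a difference. Endpoint 7 may follow, because a diagnosis of delirium or FLACC above 3 triggers the remedial drugs.

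**Working it through.** The plan gives no figure of its own on this point, so there is nothing to reproduce. The check has two parts.

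**1. What the schedule guarantees.** Let d be the minutes from PACU arrival to awakening.

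- Required awake observation at the stated minimum = max(0, 30 − d). This gives 30 min at d = 0, 20 at d = 10, 10 at d = 20, and none at d ≥ 30.
- Shortest awake stay before discharge: the third MOAA/S score of 5 comes 10 min after the first, and the second Aldrete score 3 min after the first Aldrete score, so 10 + 3 = about 13 min. Every child is therefore awake in PACU for some time, but once 30 min have passed since arrival the text does not require PAED or FLACC during it.

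**2. What this could do to the comparison.** The documents give no delirium rate, onset time, waking time or arrival time. All of the following are assumptions:

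- true delirium 25% in both arms, with onset 0–15 min after waking;
- waking time after drug stop lognormal with log-SD 0.5; median 15 min in Group P and 20, 25 or 30 min in Group R;
- PACU arrival at a median of 12 min after drug stop;
- delirium with onset after scoring ends is counted as absent.

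Group R is made the later arm only for illustration. With waking time w, arrival time a and onset u after waking, delirium is detected if w + u ≤ a + 30. If scoring runs to the earliest discharge, it is detected if w + u ≤ max(a + 30, w + 13).

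Share waking after the window has closed, with arrival at 12 min so that the window ends at 12 + 30 = 42 min:

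- Group P: 1 − Φ(ln(42/15)/0.5) = 1 − Φ(2.06) = 2%.
- Group R: 1 − Φ(ln(42/20)/0.5) = 7%; 1 − Φ(ln(42/25)/0.5) = 15%; 1 − Φ(ln(42/30)/0.5) = 25%.

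Distortion of the observed difference in delirium, Group R minus Group P, in percentage points, by simulation:

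| Scenario | R median 20 min | 25 min | 30 min |
|---|---|---|---|
| Same 12-min median arrival in both arms, scoring stops at 30 min | −2.3 | −5.3 | −8.5 |
| Group R arrival later by the same minutes as its median waking, scoring stops at 30 min | −0.9 | −2.0 | −2.9 |
| Arrival proportional to each child's waking time, scoring stops at 30 min | about 0 | about 0 | −0.2 |
| Same 12-min median arrival, scoring to earliest discharge | −0.4 | −1.0 | −1.4 |

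The −8.5 lies between −8.3 and −8.6 depending on the spread assumed for arrival. If waking and arrival times are the same in both arms, the distortion is zero.

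A second onset model gives the loss at a given d. Take delirium of 25% within 30 awake minutes and onset after awakening exponential with mean m of 5 to 15 min. Expected detected delirium with t awake minutes scored is 25% × (1 − e^(−t/m)) / (1 − e^(−30/m)). If scoring stops at 30 min from arrival, this is 21–25% at d = 10, 14–22% at d = 20 and 0% at d = 30. If scoring runs to earliest discharge (13 awake minutes), it is 17–23% at d = 20 or d = 30.

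**The case against.** The strongest reply is that 30 min is a floor. The endpoint is incidence in PACU, no child leaves without confirmed awakening, and a blinded attending is present who must decide on treatment for delirium and pain anyway. Sites may well score past 30 min, and nothing says that a child asleep at that time counts as free of delirium. This stands as a limit on size and certainty. It does not remove the point, because the article does not require the further scoring, and three centers may stop at different times.

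The second reply is that the delay that matters runs from arrival to awakening, not from drug stop to awakening. Arrival follows extubation, which may also come later in a slower-waking arm. This stands too: the second and third rows of the table show the distortion shrinking to 3 points or less, or nearly vanishing.

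Third, a reader might infer from the 1-h flumazenil provision that remimazolam is the slower arm and that its delirium rate is therefore biased downward. The documents do not support that. The provision is a contingency, not an expected waking time, and nothing in the article states which arm wakes later after arrival. The downward direction also assumes that a sleeping child is recorded as negative, which the article does not specify.

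Finally, the full protocol may fix the stopping time, and an article may leave such detail out. But the article does state an anchor and a minimum, and it is that stated rule which guarantees unequal awake time. If the full protocol already carries scoring to discharge, only the wording needs aligning.

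**Conclusion.** The point holds as a conditional weakness in the ascertainment of secondary endpoint 6, and possibly 7. The required window is tied to an event that does not imply wakefulness, so guaranteed awake observation falls one minute for each minute of sleep after arrival and reaches zero at 30 min. Incidence may be underestimated in the arm that wakes later after arrival, provided that the arms differ in that delay, that sites stop at or near the minimum, and that sleeping children count as negative.

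Under the assumptions shown, the distortion ranges from about 0 to about 8.5 points. The upper end needs all of these together: the same 12-min median arrival in both arms, a median waking time of 30 against 15 min, and scoring stopped at 30 min. The documents establish neither an actual bias nor its direction. The success endpoint is settled before PACU, so the primary analysis and the sample size of 192 are untouched. This is a cheap improvement worth making, not a fault that threatens the trial's main conclusion.

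**What to change.** State in section 2.4.4 that PAED and FLACC are recorded every 5 min from PACU arrival until the later of (a) 30 min after arrival and (b) the time the PACU discharge criteria are met, in both arms. Those criteria already require three consecutive MOAA/S scores of 5. In section 2.5, define the incidence of delirium and of moderate or severe pain over that window.

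It must be the later of the two times. A rule that let scoring stop as soon as discharge criteria were met would cut a child awake on arrival from 30 guaranteed minutes to about 13. With the later time, the guaranteed awake observation becomes max(30 − d, about 13), so no child gets less than now, and one with d ≥ 30 goes from none to about 13 min. It does not fully equalise awake time: the remaining distortion is 0.4 to 1.4 points in the last row of the table.

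The cost is a few extra scores in slow-waking children, taken by the blinded attending who is already there for the MOAA/S and Aldrete assessments. No treatment rule changes.

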#### 2.4.5 Postoperative follow-up

Regular postoperative follow-up will be carried out for the included pediatric patients *via* telephone or subsequent visit at least 24 h after the end of the surgery. Collected data will include vital signs, concomitant medication, and postoperative laboratory tests (Complete blood count, coagulation and serum biochemical) compared with preoperative data to assess the safety of the investigational drugs and to document adverse events. Furthermore, participants will be followed up with again on day 3 postoperative with parents or legally authorized representatives asked by telephone to complete the evaluation of any negative behavior changes using the Post-Hospitalization Behavior Questionnaire for Ambulatory Surgery (PHBQ-AS) (Jenkins et al., 2015) (Supplementary Table S4)—a parental report measure used to assess negative behavior change after hospitalization, consisting of 11 items on 1-5 score. Each item will have a ‘Not Applicable’ option scoring 3 to avoid problems with missing data. The PHBQ-AS score will be calculated for each respondent as the mean score of all individual items answered on the questionnaire. A score above 3 will indicate the presence of negative behavioral change, a score equal to 3 will indicate no behavioral change, and a score below 3 will indicate an improvement in behavior.

### 2.5 Outcomes

The primary endpoint will be the incidence of the successful induction and maintenance of anesthesia. Successful anesthesia induction will be defined as LoC being reached without the use of remedial sedative drugs during the induction period. Successful anesthesia maintenance will be defined as neither need for rescue sedative medication nor discontinuity of investigational drugs during the maintenance period.

The secondary endpoints will include 1) time to LoC: the time interval from an initial dose of investigational drugs to the first MOAA/S score ≤1; 2) usage of additional sedative drugs during the induction period; 3) the BIS value before dose, at LoC, after tracheal intubation and during the maintenance of anesthesia (LoC to end of the investigational drugs); 4) awakening time: the time interval from the end of investigational drugs to the first of 3 consecutive MOAA/S scores of 5; 5) extubation time: the time interval from discontinuation of investigational drugs to extubation; 6) the incidence of ED, moderate and severe pain (FLACC scale >3) in PACU; 7) usage of remedial drugs in PACU; 8) PACU discharge time: the time interval from the end of investigational drugs to the first of 2 consecutive modified Aldrete score ≥9; 9) parental and anesthesiologists satisfaction; and 10) the incidence of negative behavior change at day 3 after surgery.

Safety endpoints will include frequency, causality, and severity of adverse events (AEs) in each treatment arm. Grading of AEs will be according to Common Terminology for Adverse Event (CTCAE), Version 5.0 criteria. Injection site pain, fluctuations in blood pressure or heart rate, and the use of vasoactive agents will be recorded. Postoperative nausea and vomiting (PONV), delayed awakening from anesthesia, and respiratory depression will also be collected.

Detailed information about surgery will be collected: name of surgery, length of surgery, intraoperative bleed loss, the total maintenance dose of study drugs (remimazolam or propofol) and remifentanil, total cumulative additional consumption, frequency of fentanyl and cis-atracurium, and usage of perioperative concomitant medication.

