Before anesthesia induction, peripheral venous access will be established and the following vital signs will be monitored throughout the study: continuous electrocardiogram (ECG), heart rate (HR), respiratory rate (RR), pulse oxygen saturation (SpO_2_), and non-invasive blood pressure (NIBP) which will be adjusted by measuring at 1-min intervals until achieving endotracheal intubation and every 5min thereafter. The Bispectral Index (BIS, Aspect Medical Systems-Covidien) pediatric sensor strip will be applied on the forehead of every child, and the BIS value will be recorded before the dose, at LoC, after tracheal intubation and thereafter at 5-min intervals. Subsequently, all pediatric patients will be pre-oxygenated for several minutes in 100% oxygen at a flow rate of 3 L/min followed by a single dose of fentanyl 3 μg/kg (Yichang Humanwell Pharmaceutical, China) intravenously. About 3 min later, all pediatric patients will randomly receive an initial intravenous dose of remimazolam 0.3 mg/kg in Group R or propofol 2.5 mg/kg in Group P for the induction of anesthesia, the injection time ≤60s. The investigator will administer an additional intravenous dose of remimazolam 0.1 mg/kg in Group R or propofol 1.0 mg/kg in Group P under such condition that the child will not achieve the loss of consciousness (LoC: MOAA/S score ≤1) within 60s, the injection time ≤30s. In both groups, the additional dose will be limited to single-use only. If LoC still does not occur within 1 min after the additional dose, propofol 1.0 mg/kg as the remedial sedative drug will be administered repeatedly by intravenous injection until MOAA/S score ≤1, in which general anesthesia will be maintained using isoflurane inhalation instead of propofol or remimazolam.

After reaching LoC without the use of the remedial sedative drug, the researcher will immediately begin taking an intravenous infusion of remimazolam at an initial rate of 2 mg/kg/h in Group R or propofol at an initial rate of 8 mg/kg/h in Group P and remifentanil (Yichang Humanwell Pharmaceutical, China) at an initiation rate of 0.25 μg/kg/min in both groups, while administering cis-atracurium 0.2 mg/kg intravenously. Tracheal intubation will be facilitated to provide assisted ventilation after approximately 3 min.

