#### 2.4.3 Maintenance of general anesthesia

After tracheal intubation is completed, parameters of mechanical ventilation using volume-controlled or pressure-controlled ventilation mode with 50% oxygen/air mixture will be set according to age and ideal body weight to maintain PetCO2 between 35 and 45 mmHg. Anesthesia will be maintained with a constant infusion rate of remimazolam 1–3 mg/kg/h in Group R or propofol 4–12 mg/kg/h in Group P, and remifentanil 0.1–0.5 μg/kg/min in both groups.

The infusion rate of drugs will be adjusted within the prescribed maintenance dose range in the context of the changing intensity of surgical stimuli as primary guidance and the BIS value as secondary guidance to maintain an appropriate depth of anesthesia. Remedial sedative and/or analgesic drugs will be given to children suffering from an inadequate depth of anesthesia defined as the appearance of at least one of the following signs: patient movement, sweating, tears, hypertension and tachycardia (systolic blood pressure (SBP) and HR exceeding 25% of the baseline value for more than 5min), or clear and substantial elevations in SBP or HR, followed by discontinuing the investigational drugs and switching to continuous inhalation of isoflurane. The choice of remedial sedative and/or analgesic medications and dosage will be determined by the investigator. If hemodynamic instability persists in either group, additional vasoactive agents (e.g., esmolol or urapidil) will be administered at the investigator’s discretion. In both groups hypotension (SBP <70 mmHg + (2 x age in years) for a further 5 min) and bradycardia (HR < 70 bpm for a further 5 min) will be treated with ephedrine/phenylephrine and atropine, respectively, and the investigator will decide whether to discontinue the study drugs If necessary.

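### For children switched to isoflurane, the awakening, extubation and PACU discharge clocks start too early and count the rest of the operation as recovery (minor)

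*Protocol article*

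**What the plan says.** Section 2.5 of the protocol article gives full operational definitions of three secondary recovery endpoints, all with the same starting point:

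- "awakening time: the time interval from the end of investigational drugs to the first of 3 consecutive MOAA/S scores of 5"
- "extubation time: the time interval from discontinuation of investigational drugs to extubation"
- "PACU discharge time: the time interval from the end of investigational drugs to the first of 2 consecutive modified Aldrete score ≥9"

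Two earlier sections describe how study drug can stop before the operation ends. After failed induction (section 2.4.2) rescue propofol is given, "in which general anesthesia will be maintained using isoflurane inhalation instead of propofol or remimazolam". When anesthesia is too light during maintenance (section 2.4.3), remedial drugs are given, "followed by discontinuing the investigational drugs and switching to continuous inhalation of isoflurane".

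For everyone else, section 2.4.4 sets the stopping point: "All the drugs will be discontinued at the end of the surgery". Section 2.7 puts every randomized and treated child in the full analysis set. It compares continuous endpoints by t-test or, if non-normal, by Mann-Whitney with a Hodges-Lehmann estimate.

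**The concern.** A recovery time should run from the moment the child is allowed to wake. For a child who completes on study drug, the end of study drug is that moment. For a child switched to isoflurane it is not: study drug ends during the operation, or at induction, and the child is deliberately kept anesthetized until surgery is over. The three recorded times then equal the remaining surgery plus recovery from isoflurane.

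The values of individual switched children on three secondary endpoints are therefore wrong by construction. If one arm fails more often than the other, that arm's recovery would look slower than it is. Staff who sensibly used the isoflurane stop time instead would be recording a different quantity under the same definition, possibly differently across the three centers.

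**Working it through.** **Do the sections conflict?** Section 2.4.3 describes the mid-operation switch as discontinuing the investigational drugs and then giving isoflurane, so isoflurane is not an investigational drug in the protocol's own usage. Section 2.5 starts the clocks at that discontinuation. The full analysis set retains switched children. The available-case rule does not remove them, because their times are recorded, not missing. The article states no other clock for them.

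**The plan's own figure.** The sample size rests on 98% success in both arms, an 8-point margin, one-sided 0.025, 90% power and 3:1 allocation. Controls: (1.960 + 1.282)² × 0.98 × 0.02 × (1 + 1/3) / 0.08² = 42.9, so 4 × 42.9 = 171.6 in total, against 171 stated. This point does not affect it.

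**How many children?** Take each primary-endpoint failure as a switched child.
- Group R: 0.02 × 144 = 2.88
- Group P: 0.02 × 48 = 0.96
- Total: 3.84, about 4 of 192
- P(at least one) = 1 - 0.98^192 = 0.979

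**How wrong is a switched child's value?** The document gives neither awakening times nor surgery length. Assume lognormal awakening with median 20 min and log-SD 0.35 in both arms. The true mean is 20 × exp(0.35²/2) = 21.3 min. Assume the remaining surgery at the switch is uniform:
- 10 to 90 min (mean 50): mean recorded time about 71 min
- 5 to 45 min (mean 25): about 46 min
- 30 to 150 min (mean 90): about 111 min

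**What happens to the group comparison?** The simulation used 1,500 trials per setting, 144 vs 48 children, no true difference, and 10 to 90 min added for a fixed number of switched children. Bias is the Hodges-Lehmann estimate (R minus P) with the added time, minus the estimate without it. The grid column rounds times up to the 5-min MOAA/S schedule. Extubation time is not on that grid, so the continuous column applies to it.

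| Failures, R vs P | Bias, continuous (min) | Bias, 5-min grid (min) | Wald lower limit, primary endpoint |
|---|---|---|---|
| 3 vs 1 | 0.00 | 0.00 | -4.67% |
| 9 vs 3 | -0.01 | -0.01 | -7.91% |
| 7 vs 2 | +0.09 | +0.01 | -7.35% |
| 6 vs 1 | +0.27 | +0.09 | -7.28% |
| 6 vs 0 | +0.51 | +0.21 | -7.43% |
| 3 vs 3 | -0.53 | -0.26 | -3.07% |
| 3 vs 5 | -1.10 | -0.67 | -0.62% |

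Reruns agree to within a few hundredths of a minute. At 6 vs 0, the other two ranges of remaining surgery give +0.46 and +0.52 min (continuous).

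The unequal extremes are unlikely at 98% success in both arms. Six or more failures in Group R with none in Group P has probability 0.027. Five or more of 48 in Group P has probability 0.0027.

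**If means were compared instead.** The shift is the share switched times the mean remaining surgery. At 6 vs 0 it is 6/144 × 50 = +2.1 min. At 3 vs 5 it is 3/144 × 50 - 5/48 × 50 = -4.2 min. Section 2.7 reserves the t-test for normally distributed data, which outliers of this kind make unlikely.

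**Caution on the last column.** Section 2.7 names no interval method, so a pass at -8% here means a pass by Wald only. At 6 vs 0 the Newcombe limit is -4.17% - 4.63% = -8.79% (4.63 points is the distance from 95.83% down to its Wilson lower limit of 91.21%), which fails.

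**The case against.** The strongest reply is that handling of rescued children is intercurrent-event handling, which a condensed article may leave to the full protocol or analysis plan. That would answer a complaint about missing detail. It does not answer this one, because the article states complete definitions and those definitions give the wrong starting point under its own rescue rules.

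A second reply is contextual. Section 2.4.4 speaks of drugs stopping at the end of surgery and then of MOAA/S scoring after study drug is removed, so staff would naturally begin there, and nobody would score a child under isoflurane. This softens the reading of the procedure but does not alter the interval that section 2.5 defines.

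A third reply is that nothing visible happens at the design assumptions. That stands: with equal failure rates the between-group shift is about zero.

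A reader might also infer more than the document supports:
- **Biased recovery comparison.** Bias needs unequal failure rates, and its sign follows whichever arm fails more. The document gives no reason to expect either direction.
- **The BIS window is also wrong.** Section 2.5 reports BIS "during the maintenance of anesthesia (LoC to end of the investigational drugs". Ending that window with study drug is appropriate, since it keeps isoflurane readings out.
- **The MOAA/S schedule and the 1-hour flumazenil check in section 2.4.4 need rewording.** No harm from that wording is shown. Flumazenil also requires that the child has not roused.
- **A trial with any of these failure counts would still meet its margin.** That depends on the interval method, as the 6 vs 0 case shows.

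**Conclusion.** The point holds as a minor error in three endpoint definitions, confined to children switched to isoflurane. Definitions for children who complete on study drug are correct. About 4 of 192 children are expected to be affected at the planned success rate. The primary endpoint and the sample size are not touched. The Hodges-Lehmann shift between groups is about zero at equal failure rates, roughly 0.5 min or less in most unequal cases, and about -1.1 min at 3 vs 5.

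The number of children rests on the document's 98% and on treating each failure as a switch. The minutes rest entirely on assumed awakening and surgery times and are illustrative. That the clock starts in the wrong place for these children follows from the text alone.

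**What to change.** In section 2.5, define time zero for awakening, extubation and PACU discharge as the end of all hypnotic administration, whether study drug or isoflurane, with the end of surgery as fallback if that time is not recorded. Values for children who complete on study drug do not change.

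Add a descriptive report of the three times in children who completed on study drug. The corrected times in switched children will reflect isoflurane recovery and not that of remimazolam or propofol. Keep this report supportive, because completing on study drug is itself a post-randomization event.

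The cost is one sentence in the endpoint definitions and one more recorded item, the isoflurane stop time. The fallback also needs the clock time at which surgery ends; the listed data items give only its duration ("Detailed information about surgery will be collected: name of surgery, length of surgery"). The BIS window, the MOAA/S schedule and the flumazenil instruction can stay as they are.
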